**Table 2 Tab2:**
[figure not shown]
Schedule of enrolment, intervention, and assessments (cf. Chan et. al., [36])

### Sample size

Previously, we have experienced a participation rate among eligible industrial workers of 84%, followed by a response rate of 87% of those participating [37]. At present, management in the participating organization has estimated that 110 workers will be eligible for the present study. Based on our previous experience, we assume that 80% will be willing to participate in our study (i.e., 88 workers) and that 20% will be lost to follow up. Thus, assuming that 70 participants, organized in clusters with an average size of *n* = 4 (range *n* = 2 to *n* = 7), will complete the study, we may estimate the detectable effect size in a cluster randomized controlled design as follows:

In our previous feasibility study among industrial workers [16], we found that low back pain intensity was, on average, 3.7 points (on a 0–10 scale) with a total variance between workers of 10.6. This total variance will be reduced with repeated measurements over days in each subject. Within-subject (between-days) variance was 1.6, or 15% of the total variance (between-subject and within-subject) of low back pain. If we repeat measurements for 5 days, the within-subject variance will be reduced to 0.3, resulting in an estimated total variance of 9.3. Based on this, we can – given the sample size stated above, i.e. *n* = 70 – expect to be able to detect a 1.5 point difference between groups in low back pain intensity, at a significance level of 0.05, a power of 0.80, and a cluster size of 4 (the average size).

The effect on low back pain intensity from redesigning physical behaviors at work is unknown. In our feasibility study, we found a mean difference of 1.1 in low back pain intensity between usual and redesigned workdays [16]. However, we cannot draw any firm conclusion about the expected effect size from that study due to the difference in study design, the limited sample size (*n* = 14) and, hence, the large uncertainty in data. Nevertheless, reducing low back pain intensity by 1.5 is likely to be a meaningful clinical and work-related change [38]. Therefore, we find it meaningful to conduct the present study despite its uncertainties.

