**Methods:**

Our implementation plan consists of educating work teams, organizing implementation meetings, and providing feedback to workers. Three meetings with a preselected local workplace group will be scheduled. The first meeting educates the group to use a planning tool by which work can be planned to have ‘just right’ physical behaviors. The second and third meetings will focus on supporting implementation of the tool in daily work. An expected 28 clusters of work teams across two participating production sites will be randomized to either intervention or control group. Data collection will consist of 1) questionnaires regarding work and musculoskeletal health, 2) wearable sensor measurements of the physical behavior, and 3) assessment of general health indicators, including BMI, blood pressure, and fat percentage. The primary outcome is musculoskeletal health, measured by low back pain intensity, and secondary outcomes are 1) physical behaviors at work, 2) accumulated time in long bouts of sitting, standing, and being active and 3) perceived fatigue and energy during work. Furthermore, implementation and cost of the intervention will be evaluated based on questionnaires and data from the planning tool completed by the workers.

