### Trial design

The Goldilocks Work intervention will use two parallel groups, with an allocation ratio of 1:1. Work teams consisting of 1–7 workers, as already organized at the workplace, will be randomly allocated to either an ‘intervention group’ receiving the intervention, or a ‘control group’ performing work as usual.

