We designed a general planning tool (i.e., a modification that could likely be implemented, step 4 in Fig. 1) in Excel (Microsoft Office Professional Plus 2016) with the purpose of providing workers with a specific instrument by which they could organize their work tasks. The purpose of this tool is to have workers modify their jobs towards the ‘just right’ physical behavior. To make the tool implementable and applicable for workers, it will be tailored to their work context. Prior to the intervention, a member from our research team will involve the work environment representatives to identify all relevant work tasks, and then have them determine the typical physical behavior for each task as either sitting, standing or active. To ensure that the tool properly reflects the work context at any time, work tasks can be added or modified (e.g. by changing their predefined physical behavior) during the intervention, based on feedback from workers and the local workplace group. At any time, the planning tool includes the existing work tasks, so that workers can select them from a drop-down list, and plan their working day. In the present study, the planning tool partitions the workday into six blocks of approximately one hour each. The objective for each work team of 1 to 7 workers is to rearrange and swap work tasks in production on a given day until everyone has the best possible ‘Goldilocks index’. The ‘Goldilocks index’ will be generated by the general tool, ranging between 0 and 100 (where 100 is the best score possible) and based on how close the plan is to being ‘just right’. To guide the workers, the ‘Goldilocks index’ is color-coded: red if the index is < 50 points, yellow if the index is 50–79, or green if the index is ≥ 80.

We summarized the decisions made in the 4-step process in a program logic (Fig. 2). The program logic is a visual representation of the intended changes in the intervention program and activities, how they are expected to change physical work behavior, and how that will, eventually, improve the health-related goal [28]. The program logic was used as a simple illustration to share with stakeholders [28] and to guide the planning of the intervention, deciding when to do what, and with whom (Fig. 3).

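### The sample size section gives the 70 expected completers an average cluster size of 4 and a range of 2–7, but 28 clusters with 70 completers average 2.5, and team size is stated elsewhere as 1–7

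*Protocol article*

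**What the plan says.** The protocol article describes the randomised unit in four places.

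- **Abstract, Methods:** "An expected 28 clusters of work teams across two participating production sites" are to be randomised.
- **Trial design:** the units are "Work teams consisting of 1–7 workers, as already organized at the workplace".
- **Development of the intervention, Step 4:** the planning tool is described for the same range: "The objective for each work team of 1 to 7 workers" is to arrange the day's tasks so that everyone scores as well as possible.
- **Sample size:** management "has estimated that 110 workers will be eligible for the present study". Participation of 80% gives 88 workers, and 20% loss leaves 70. The calculation then proceeds by "assuming that 70 participants, organized in clusters with an average size of" 4, and these 70 are described as "organized in clusters with an average size of *n* = 4 (range *n* = 2 to *n* = 7), will complete the study". The detectable difference of 1.5 points (alpha 0.05, power 0.80) is said to use a cluster size of 4, identified as the average.

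**The concern.** Two statements about the unit of allocation do not fit together.

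First, the range. Teams are 1–7 workers in two places and 2–7 in the sample size section. Non-participation and dropout can lower the smallest cluster but cannot raise it from 1 to 2, and no stated criterion removes one-worker teams.

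Second, the average. The sample size section attaches a size of 4 to people who complete the study, after two rounds of loss. That cannot be squared with 28 clusters and 70 completers.

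The average is a working input: cluster size sets the design effect and, with the total, the implied number of clusters. Anyone checking the detectable difference would take about 18 clusters of 4, where the recruitment plan gives 28 clusters of 2.5.

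**Working it through.** **Inputs from the protocol.** Eligible 110, participation 80%, loss 20%, completers 70, cluster size 4, variance 9.3, alpha 0.05, power 0.80, detectable difference 1.5 (all Sample size); 28 clusters (abstract); 1:1 allocation (Trial design), so 35 completers per arm.

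**Assumed.** Two-sided test; ICC 0 to 0.20, because none is given; the size distribution in step 5.

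**1. The plan's own figures.**
- 110 × 0.8 = 88, and 88 × 0.8 = 70.4, so the 70 reproduces.
- 10.6 − 1.6 + 1.6/5 = 9.32, so the variance of 9.3 reproduces.
- Detectable difference = (1.960 + 0.842) × √(2 × 9.3 × DE / 35). With DE = 1 (no clustering) this is 2.04, so the 1.5 does not reproduce from the stated inputs. That is a separate matter, taken up only under the objection and the fix.

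**2. Workers per cluster with 28 clusters.**
- Eligible: 110/28 = 3.93
- Participants: 88/28 = 3.14
- Completers: 70/28 = 2.50

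Only the first rounds to 4.

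**3. Clusters implied by size 4.** 70/4 = 17.5, against 28. Conversely, 28 × 4 = 112, close to the 110 eligible workers and far from 70.

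**4. Effect on the calculation, equal cluster sizes.** DE = 1 + (m − 1) × ICC. The detectable difference scales with √DE.

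| ICC (assumed) | DE, m = 4 | DE, m = 2.5 | √ ratio | Difference, m = 4 | Difference, m = 2.5 |
|---|---|---|---|---|---|
| 0 | 1.00 | 1.00 | 1.00 | 2.04 | 2.04 |
| 0.05 | 1.15 | 1.075 | 1.03 | 2.19 | 2.12 |
| 0.10 | 1.30 | 1.15 | 1.06 | 2.33 | 2.19 |
| 0.20 | 1.60 | 1.30 | 1.11 | 2.58 | 2.33 |

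Using 4 in place of 2.5 therefore overstates the result by 3%, 6% and 11%.

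**5. Effect with unequal sizes.** Replace m by m(1 + CV²). Suppose eligible team sizes are uniform on 1–7 (mean 4, variance 4) and each worker completes independently with probability 0.8 × 0.8 = 0.64.
- Mean completers per team = 0.64 × 4 = 2.56.
- Variance = 0.64² × 4 + 0.64 × 0.36 × 4 = 1.638 + 0.922 = 2.56.
- CV = √2.56 / 2.56 = 0.625.
- Effective size = 2.56 × (1 + 0.625²) = 3.56.
- DE at ICC 0.05 / 0.10 / 0.20 = 1.128 / 1.256 / 1.512.
- √(1.15/1.128), √(1.30/1.256), √(1.60/1.512) = 1.01, 1.02, 1.03.

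The overstatement falls to about 1%, 2% and 3%.

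**The case against.** **The error is harmless.** At a fixed total of 70, a larger assumed cluster size gives a larger design effect, so using 4 does not flatter the power. With strongly varying sizes, 4 is close to the effective size of about 3.6. This stands, and it limits the point to a correction of a stated input. It does not make the text right: nothing in the protocol says that 4 is a size-weighted figure, and the cluster count it implies is still not 28.

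**Whole teams might drop out.** If refusal and loss removed entire teams, 28 × 0.64 = 17.9 teams of about 3.9 would remain, and the sample size text would be coherent. But Assignment of interventions has workers asked and consenting one by one, and the participation rate is given for workers. The expected cluster count would then also have to be restated as about 18.

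**Stronger readings that the protocol does not support.**
- A reader might infer that one-worker teams cannot use the planning tool and so dilute the intention-to-treat effect. Step 4 explicitly covers teams of one. A lone worker can select tasks from the list, reorder the day and receive an index; only swapping with a colleague is lost. The number of one-worker teams, if any, is not given, so no dilution can be claimed or sized.
- A reader might take it as fact that 4 is the size of eligible teams. It is the only stage that matches, but this remains an inference.
- A reader might conclude that the stated 1.5 points is too large by 3–11%. That is the effect of this one input only. On the stated variance and 35 per arm, 1.5 is smaller than the formula gives even without clustering (2.04), for reasons unrelated to cluster size.

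**Conclusion.** The point holds as a consistency error in a stated design input. Two facts need no assumption: the team-size ranges (1–7 and 2–7) contradict each other, and 28 clusters with 70 completers average 2.5, not 4.

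The consequence is small and conservative. The clustering inflation of the detectable difference is overstated by nothing at ICC 0, by 3–11% at an assumed ICC of 0.05 to 0.20 with equal sizes, and by about 1–3% under the assumed strong size variation. The true figure depends on an ICC and a size distribution that the protocol does not give. The error neither inflates the claimed power nor calls the design into question.

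**What to change.** - Use one team-size range in Trial design, Step 4 and Sample size. If one-worker teams exist, the range is 1–7 throughout, and the completer range should allow for losses.
- In Sample size, state 28 clusters and give the mean size at each stage: about 3.9 eligible workers, 3.1 participants and 2.5 completers.
- State the assumed ICC; without it the clustering adjustment cannot be checked.
- Recompute and restate the detectable difference for 28 clusters of about 2.5 completers, with size variation through m(1 + CV²), taking the CV from the actual team list.

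There is no need to combine one-worker teams. The protocol uses teams as they already exist, names no partner team for a lone worker, and reports under Study setting that implementation was already under way. Merging would also change the count of 28.

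The cost is wording and one calculation, with no extra participants or data. The authors should expect the recalculation not to return 1.5 from the stated variance and 35 per arm, and should state any further assumption on which that figure rests.

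### The 1.5-point detectable difference at 80% power does not follow from variance 9.3 and 70 completers in total; those inputs give about 2.0 points before clustering

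*Protocol article*

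**What the plan says.** The Sample size section starts from 110 eligible workers. It assumes that 80% take part (88) and that 20% of these are lost, which leaves 70 completers for the whole trial.

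For the variance it takes low back pain intensity from the feasibility study, "with a total variance between workers of 10.6". Averaging over five days reduces the within-subject part, "resulting in an estimated total variance of 9.3". On this basis, and with n = 70, it says that the trial can "expect to be able to detect a 1.5 point difference between groups in low back pain intensity, at a significance level of 0.05", with "a power of 0.80, and a cluster size of 4 (the average size").

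The same section then calls a 1.5-point reduction likely to be meaningful and concludes that the study is worth running despite its uncertainties.

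Three other places bear on the calculation:
- Trial design sets two parallel groups at 1:1 and describes "Work teams consisting of 1–7 workers, as already organized at the workplace". The Sample size section gives a range of 2 to 7.
- The abstract's Methods state: "An expected 28 clusters of work teams across two participating production sites will be randomized".
- Primary outcome measure defines the outcome as the between-group difference in change from baseline to 12 weeks.

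**The concern.** The section gives every main input and the result, so the result can be checked. The variance is large (SD about 3.05 on a 0–10 scale) and there are only 35 completers per arm. A detectable difference of half an SD looks too small for that size, and clustering should make it larger still.

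The 1.5 carries weight because it serves as both what the trial can detect and what would be meaningful. If the power for 1.5 is well below 80%, a real benefit of that size could easily be missed. Readers told that power was 80% could then take a null result as evidence against a meaningful effect.

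**Working it through.** **Inputs.** From Sample size: total variance 10.6, within-subject variance 1.6, five days, 70 completers, alpha 0.05, power 0.80, cluster size m = 4. From Trial design: 1:1 allocation, so 35 per arm. Assumed: a two-sided test, because sidedness is not stated, and ICC values, because none is given.

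**Variance.** 10.6 − 1.6 + 1.6/5 = 9.32. The article's 9.3 is reproduced.

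**Detectable difference.** MDD = (1.960 + 0.842) × √(2 × 9.3 × DE/n per arm), with DE = 1 + (m − 1) × ICC.

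Without clustering, the standard error is √(2 × 9.3/35) = 0.729 and the MDD is 2.802 × 0.729 = **2.04**. A t-test version gives 2.07. The stated 1.5 is not reproduced.

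Power for 1.5 is Φ(1.5/0.729 − 1.96) = Φ(0.098) = **54%** (53% by t-test).

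**With clustering** (35 per arm, ICC assumed):

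| m | ICC | DE | MDD | Power for 1.5 |
|---|---|---|---|---|
| any | 0 | 1.000 | 2.04 | 54% |
| 4 | 0.05 | 1.150 | 2.19 | 48% |
| 4 | 0.10 | 1.300 | 2.33 | 44% |
| 2.5 | 0.05 | 1.075 | 2.12 | 51% |
| 2.5 | 0.10 | 1.150 | 2.19 | 48% |

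**Sample needed for 1.5 at 80% power.** 2 × 7.849 × 9.3/1.5² = 64.9, so 65 per arm (130 in total) before clustering. At ICC 0.05 and m = 4 this is 64.9 × 1.15 = 74.6, so about 75 per arm.

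**Other readings tried, variance 9.3, no clustering:**
- One-sided alpha of 0.05, 35 per arm: MDD 1.81, power for 1.5 of 66%.
- All 88 participants with no dropout (44 per arm), two-sided: 1.82.
- All 110 eligible workers completing (55 per arm), two-sided: 2.802 × √(18.6/55) = 1.63.
- 70 per arm: 1.44, or 1.51 at ICC 0.03 and m = 4. This needs 140 completers, more than the 110 eligible.
- Leaving out the factor 2 for a two-group contrast with 35 per arm: 2.802 × √(9.3/35) = 1.44, numerically the same as 70 per arm.

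**Baseline information.** For 70 in total and no clustering, an MDD of 1.5 needs a variance of (1.5/2.802)² × 35/2 = 5.02.
- Change score, variance 2 × 9.3 × (1 − r): r = 0.73.
- Covariance adjustment (ANCOVA), variance 9.3 × (1 − r²): r = 0.68.
- At DE 1.15 these become 0.77 and 0.73.
- A change score with r = 0.5 gives 2.04 again, and a lower r gives more.

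**Cluster inputs.** 70 completers in teams of 4 is 70/4 = 17.5 teams. With 28 teams it is 70/28 = 2.5 completers per team. The eligible workforce gives 110/28 = 3.9 per team.

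**The case against.** The strongest reply is that 9.3 is the variance of a single five-day mean, while the primary outcome is a change from baseline. The power of the actual analysis therefore depends on a baseline-to-follow-up correlation that the article does not give. Without clustering, power for 1.5 would be 54%, 76% and 90% for a change score at r = 0.5, 0.7 and 0.8, and 66%, 82% and 93% with covariance adjustment. The section's own variance components imply a same-person, day-to-day correlation of about 9.0/10.6 = 0.85, so a 12-week correlation near 0.7 is not ruled out. This stands as a limit on the claim: it is not shown that the trial as analysed has about 50% power. It does not rescue the text, which derives 1.5 from 9.3 and never mentions baseline adjustment or a correlation.

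Other points also stand in part:
- The cause of the error is conjecture. Using 70 per arm and dropping the factor 2 give the same number, and the article does not say which, if either, occurred.
- Power below 54% rests on assumed ICCs. A condensed article may leave the ICC to a fuller document, so its absence is not a fault in itself.
- The size of 4 fits eligible workers per team (3.9). For any positive ICC, 4 gives a larger design effect than 2.5, so this mismatch is conservative and cannot explain the optimistic 1.5.
- The 1–7 versus 2–7 range enters no calculation.
- The sample is limited by the workforce and implementation had begun at submission. The uncertainties that the section admits concern the unknown effect size, however, not the power calculation.

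**Conclusion.** The stated figure is wrong on its own inputs. Variance 9.3, 35 completers per arm, alpha 0.05 and 80% power give a detectable difference of 2.04 points, not 1.5. Two-sided power for 1.5 is at most about 54%. These are best-case values that need no ICC. Under assumed ICCs up to 0.10 with m = 4, the detectable difference rises to 2.33 and power falls to 44%. A one-sided test, full retention, or even every eligible worker completing would not reach 1.5 at 80% power on this variance.

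The conclusion assumes that 9.3 is the variance meant for the between-group comparison, as the section says. A baseline correlation of about 0.7 or more could bring the real analysis close to 1.5, but the article neither states nor uses one. The team-size and team-count discrepancies are secondary. The paragraph must be corrected because the case for running the trial relies on it.

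**What to change.** Rewrite the Sample size paragraph:

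1. State that 70 is the total, 35 per arm, and restate the detectable difference on variance 9.3 as about 2.0 to 2.3 points for an ICC range of, say, 0 to 0.10.
2. If baseline adjustment is relied on to approach 1.5, name the analysis and the correlation needed: with covariance adjustment, about 0.68 without clustering and about 0.73 at ICC 0.05 with m = 4; with a change score, about 0.73 and 0.77. Support the value chosen.
3. Reconcile the cluster inputs: 28 teams, about 3.9 eligible workers and 2.5 completers per team, and one team-size range throughout.
4. In the detailed analysis plan, which is still to be completed before analysis, it would help to say that a non-significant result will be read through its confidence interval against 1.5 points.

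This is rewording only: no extra participants and no change to conduct. The cost is a less favourable statement of what the trial can detect.

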## Methods: assignment of interventions

First, workers will be asked by a researcher if they wish to participate in the study. Workers agreeing will then sign an informed consent, and workers declining will be counted as non-participants. After signing the informed consent, workers will complete a physical assessment and following that, they will be verbally informed about their group allocation. This is necessary because we need to plan training activities with the work teams and the local workplace group. Additionally, we need to prepare the planning tool to comply with the specific work tasks of the work teams allocated to the intervention.

Due to the nature of the intervention, it is not possible to blind the workers to their allocation. Additionally, during enrolment, blinding of the assessors is not possible. However, the main outcome, musculoskeletal health, is measured through questionnaires sent out via text messages, and thus, is not affected by our inability to blind the assessors during enrolment. Furthermore, all secondary outcomes are collected with either wearable sensors or questionnaires, and will not be biased by lack of assessor blinding.

Clusters (i.e. teams) will be randomly allocated to the intervention and control groups in a 1:1 ratio. The teams will be allocated using SAS version 9.4 and the function RANUNI, which returns a number generated from a uniform distribution on the interval (0, 1) [39]. The randomization process will be performed separately for each production site, i.e., the randomization will be stratified. Clusters within a production site receiving values in the lower half of numbers drawn at that site will be assigned to the intervention, and clusters with values in the upper half will be controls. A data manager not otherwise involved in conducting the intervention will generate the allocation sequence for each production site.

Intervention and control workers will be present at all included production sites. This allocation procedure was chosen to reduce the risk of bias due to changes in contextual factors (e.g., change in management, structural changes, or supply chain challenges) during the intervention period, which have been shown to occur quite often [40]. Furthermore, it may also reduce potential bias from contextual differences that may exist between sites, such as differences in work tasks, restrictions in production complicating work planning, or how machines are operated.

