### Outcomes

#### Primary outcome measure

The primary outcome measure for the trial will be the difference between intervention and control groups in the change of low back pain intensity from baseline to follow up (12 weeks). We chose low back pain as an overall representation for musculoskeletal health (Fig. 2.), since it has a pronounced influence on both work ability [9], sick leave [10], and since it occurs in many pain patterns [35]. Pain intensity will be measured repeatedly on a numeric scale (NRS, 0–10). A question will be sent to the participants in a text message at the end of the workday for five consecutive workdays at baseline (week 1) and five consecutive workdays at follow up (week 12), asking them to rate their low back pain intensity.

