### Physical behaviors

The protocol for measuring physical behaviors will be similar to that used in previous studies [16, 19, 42]. An AX3 accelerometer (3-Axis Logging Accelerometer; Axivity Ltd., Newcastle upon Tyne, UK) will be mounted using adhesive tape (Hair-Set double-sided adhesive tape; 3 M Company, Maplewood, MN, USA) on the worker’s right thigh at the most muscular part of the quadriceps femoris, midway on the line between the anterior inferior iliac spine and the top of the patella. Workers will be asked to wear the accelerometer around the clock for five consecutive days at baseline and follow up, and will be instructed on how to change the adhesive tape if necessary. At the end of day five, the accelerometer will be returned to the research team. Data will be downloaded using the manufacturer’s software (OMGUI, Configuration and Analysis Tool). A workday will be excluded from further analysis if accelerometer recordings are available for less than 4 h. Periods > 60 min without movement will be regarded as non-wear time or sleep.

Physical behaviors will be exhaustively classified using the Acti4 software [42] into time spent sitting or lying (termed sitting below), standing (consisting of time spent standing still, or standing with slight movement), and active (consisting of time spent walking, running, stair climbing or cycling).

During all measurement days, the workers will note in a diary at what time they: 1) woke up, 2) arrived at work, 3) left work, 4) went to sleep, and 5) if the accelerometer was detached at any time during data collection. On the basis of the diaries, the continuous timeline of physical behavior data will be partitioned into periods of, 1) work, 2) leisure time awake, and 3) time in bed.

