### Questionnaires

The questionnaires consist of standard validated questions, as well as questions to describe the intervention process. At baseline and follow up we will collect information about musculoskeletal health [43], general health [44], need for recovery [45], self-assessed physical fitness [46], sickness absence, psychosocial work environment [47] and productivity [48–50]. Questionnaires using a numerical scale from 0–10 will be send at the end of the workday, for each of the first five days and the last five days of the intervention on; 1) pain, 2) fatigue and 3) energy [43]. Furthermore, customary questions will be used to collect information about participants’ use of medication and healthcare services.

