### Strengths and limitations

The 4-step procedure and participatory approach that guided the development of the program logic and the intervention is a strength of this protocol. The cluster randomized controlled design with randomization performed at each production site is a strength because it reduces potential bias. The planning tool adapted to the workers’ context is a strength because it offers an easy-to-use and practical approach for their own planning of work tasks to change behavior. The approach of feeding back information from the planning tool to the workers is also a strength that can improve the likelihood that workers’ behavior is changed [34]. Furthermore, the information collected about the implementation process is a strength because it may inform details about who did what when, and explain why things turned out as they did.

A limitation is that participants are not blinded to their allocation; this can increase the risk of selection bias. However, workers will not receive knowledge of their allocation until after they completed their eligibility screen and health check. Another limitation is the short duration of the study (i.e., 12 weeks), since it may take longer to effectively implement changes in physical behavior and thus effectively improve musculoskeletal health. However, even if the intervention is not effective, the workers and the workplace will gain valuable knowledge about their work context, the current physical behavior, and which changes that may improve workers’ health on the long term.

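### Nothing delays telling workers their arm until the five week-1 pain ratings are complete, so all or most of the primary outcome's baseline can be rated with the arm known

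*Protocol article*

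**What the plan says.** All references are to the protocol article.

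- **Disclosure.** Methods: assignment of interventions gives the order as consent, physical assessment, then disclosure: "workers will complete a physical assessment and following that, they will be verbally informed about their group allocation". The reasons given are planning of training with the teams and preparation of the planning tool. Strengths and limitations repeats the timing: "workers will not receive knowledge of their allocation until after they completed their eligibility screen and health check".
- **Blinding.** The same Methods section accepts that "it is not possible to blind the workers to their allocation". It then argues that outcomes collected by text message, questionnaire or sensor are not biased by unblinded assessors.
- **Primary outcome.** It is "the difference between intervention and control groups in the change of low back pain intensity from baseline to follow up (12 weeks"). Pain is rated on a 0–10 scale "at the end of the workday for five consecutive workdays at baseline (week 1) and five consecutive workdays at follow up (week 12").
- **Second description of the window.** Questionnaires places the daily ratings of pain, fatigue and energy "for each of the first five days and the last five days of the intervention".
- **Sensors.** Under Physical behaviors, the accelerometer is worn for five days at baseline. "At the end of day five, the accelerometer will be returned to the research team".
- **Tool release.** Under Planning tool, the link goes to intervention workers once baseline measurement is over, and tool use runs from week 3 to week 12.

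**The concern.** The disclosure rule is tied to a single visit, whereas the baseline of the primary outcome is a five-day series of self-ratings. What is sure to precede disclosure is the eligibility screen and the physical measurements (body mass index, fat percentage, blood pressure), and none of these measurements is a primary or listed secondary outcome. The pain ratings have no such protection.

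The bias argument in the article concerns assessors, but for pain the worker is the rater, and the worker has been told the arm. Unblinded ratings at week 12 cannot be avoided in this trial. Unblinded ratings at baseline can.

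Baseline is one of the two terms of the primary effect. If knowing the arm moves baseline ratings differently in the two groups, the treatment estimate moves with them. Adjusting for that baseline would condition on a variable measured after allocation was known. Analysis cannot fully repair this while it still uses that baseline.

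**Working it through.** **1. Order of events**

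| Event | Timing in the article | Source |
|---|---|---|
| Teams randomised | Before workers are invited | Participant timeline |
| Consent, then physical assessment | Day not given | Methods: assignment of interventions |
| Worker told the arm | After the assessment, with no further condition | Same section; Strengths and limitations |
| Five pain ratings | Week 1; also described as the first five days of the intervention | Primary outcome measure; Questionnaires |
| Tool link sent | After baseline measurements | Planning tool |
| Tool use | Weeks 3 to 12 | Data collection methods; Planning tool |

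No text makes disclosure wait for the fifth rating. Delaying the tool link delays the tool, not knowledge of the arm. One link is inferred: the day of the health check relative to the first text message is not given, and Table 2 and Fig. 3 are not shown. Some early ratings could precede disclosure. Nothing states that all five do, and that would fit poorly with the consent–assessment–disclosure order and with ratings on the first days of the intervention.

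**2. The plan's own figures (Sample size)**

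- Variance of a five-day mean: 10.6 − 1.6 + 1.6/5 = 9.32, which agrees with the stated 9.3.
- Detectable difference with 35 per arm, two-sided 5%, 80% power and no clustering: (1.960 + 0.842) × √9.3 × √(2/35) = 2.04, not the stated 1.5. This is a separate matter. The 1.5 points serve below only as a yardstick.

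**3. How a baseline shift enters the effect**

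Let B and F be mean pain at baseline and follow-up in the intervention (I) and control (C) arms. The change-score effect is (F_I − B_I) − (F_C − B_C). If knowing the arm shifts B_I − B_C by b and leaves follow-up unchanged, the effect shifts by −b. Its size is b, and its direction depends on the unknown sign of b. With adjustment for baseline the shift is about rho × b.

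**4. Size for assumed b** (no value is in the document)

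| b (points) | Change-score bias as share of 1.5 | Adjusted bias, rho 0.5 | Adjusted bias, rho 0.7 |
|---|---|---|---|
| 0.25 | 17% | 0.125 | 0.175 |
| 0.5 | 33% | 0.25 | 0.35 |
| 0.75 | 50% | 0.375 | 0.525 |
| 1.0 | 67% | 0.50 | 0.70 |

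**5. False-positive rate of the change-score test for b = 0.5**

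SE = √[2 × 9.3 × (1 − rho)] × √[(2/35) × (1 + 3 × ICC)], with 35 per arm and clusters of 4. Rate = Φ(−1.96 + b/SE) + Φ(−1.96 − b/SE). Rho and ICC are assumed.

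| rho | ICC | SE | Rate (nominal 0.05) |
|---|---|---|---|
| 0 | 0.10 | 1.175 | 0.071 |
| 0.5 | 0.10 | 0.831 | 0.092 |
| 0.5 | 0 | 0.729 | 0.105 |
| 0.7 | 0.10 | 0.644 | 0.121 |
| 0.7 | 0 | 0.565 | 0.144 |

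With b = 0.25, rho 0.5 and ICC 0, the rate is 0.064.

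**The case against.** **The order is not proven.** A reader might infer that baseline pain is certainly recorded unblinded. The text does not go that far, because disclosure follows the assessment at an unstated interval and the timeline exhibits are not shown. This stands: the supported statement is that all or most ratings can be given with the arm known and that no rule prevents it.

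**The article makes no claim about baseline pain.** One might read Strengths and limitations as offering the health check as sufficient protection for the outcome. It does not. It lists non-blinding as a limitation for selection bias and offers the timing in mitigation of that. The gap is that reporting bias at baseline is not addressed.

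**A single error rate would mislead.** A reader might settle on a doubling to about 10–11%. That is one case: an assumed 0.5-point shift, rho about 0.5 and no clustering. Only the range is defensible.

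**A shift present at both time points cancels.** If knowing the arm moves ratings equally in weeks 1 and 12, the change score removes it, and protecting baseline alone would leave the follow-up shift exposed. This is correct, and the one-for-one statement holds only for a baseline-only shift. It does not justify leaving baseline open, because no one can know that the two shifts match.

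**Sensor outcomes are less exposed.** One might infer the same exposure for them. Thigh accelerometry is not self-rated, intervention workers have not yet been sent the tool, and posture at work depends largely on the tasks. Some reactivity is possible, but equal exposure is not shown.

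**Early disclosure has stated reasons.** Training and tool preparation need the allocation list. They do not clearly need every worker to know the arm, because the article has the research team identify tasks together with work environment representatives.

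**Conclusion.** The concern holds as a gap in the disclosure rule: the baseline of a self-reported primary outcome is left open to knowledge of the arm, and this is avoidable. It rests on the stated order of events, not on a calculated figure.

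The sign and size of any bias are unknown. Under the assumptions shown, a baseline-only shift of 0.25 to 1.0 points biases a change-score effect by 17% to 67% of the 1.5-point target. A 0.5-point shift raises the two-sided false-positive rate from 5% to roughly 7% to 14%. Baseline adjustment reduces the bias to about rho × b but does not remove it. The documents do not support saying that every baseline rating is unblinded, that the error rate doubles, or that sensor outcomes are equally affected.

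**What to change.** **Rule.** Tell workers their allocation on one fixed date per site, or at least per team, after the scheduled fifth baseline workday and the return of the sensors, whether or not every text message was answered. Disclosure worker by worker would not do: allocation is by team, so the first member told could reveal the arm to colleagues still rating, and a worker who missed a text would never qualify.

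**Until that date.** Researchers and, where needed, work environment representatives plan from the allocation list. Any representative who is also a participant is recorded as an exception.

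**Teams already told.** Study setting says that implementation is under way, so the new rule may come too late for some or all teams. For these, record the disclosure date relative to each baseline rating. Add a sensitivity analysis that compares week-12 pain between arms without the week-1 baseline, and state that week-12 ratings remain unblinded.

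**Cost.** About one week less lead time for team training and tailoring of the tool. Week 2 lies between the baseline week and the start of tool use, but whether it is long enough must be checked against Fig. 3. Sample size and measurements do not change.
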